## Abstract

**Background:**

Patient safety is a leading item on the policy agenda of both major international health organizations and advanced countries generally. The quantitative description of the phenomena has given rise to intense concern with the issue in institutions and organizations, leading to a number of initiatives and research projects and the promotion of patient safety culture, with training becoming a priority both in Spain and internationally. To date, most studies have been conducted in a hospital setting, even though primary care is the type most commonly used by the public, in our experience.

Our study aims to achieve the following:

- Assess the registry of adverse events as an education tool to improve patient safety culture in the Family and Community Teaching Units of Galicia.

- Find and analyze educational tools to improve patient safety culture in primary care.

- Evaluate the applicability of the Hospital Survey on Patient Safety Culture by the Agency for Healthcare Research and Quality, Spanish version, in the context of primary health care.

**Design and methods:**

**Discussion:**

The most significant limitations on the project are related to selecting a tool to measure the safety environment, the training calendar of residents in Family and Community Medicine in last year of studies and the no-answer bias inherent to research conducted through self-administered surveys.

The development and application of a safety culture in the health sector, specifically in primary care, is as yet limited. Thus, identifying the strengths and weaknesses in the safety environment may assist in designing strategies for improvement in the primary care health centers of our region.

**Trial registration:**

ISRCTN: ISRCTN41911128

## Background

Present-day health care in developed countries, with its complex combination of technologies, processes and human interactions, has brought great benefits to patients owing to its greater effectiveness. However, this fact, coupled with changing patient characteristics-patients are older, with greater morbidity and require more complex approaches-means that health care entails greater risks and a greater likelihood of causing damage to the patient.

Health care has sought to ensure that diagnostic and therapeutic processes received by patients do not cause them greater harm or injuries than the ailment itself, in an equilibrium that is beneficial to properly managing the process. But even though there has been clear concern for the negative effects of health care, it was not until the appearance of the report by the Institute of Medicine (IOM) *To Err is Human *[1] and the creation by the World Health Organization (WHO) of the World Alliance for Patient Safety [2] that this issue captured the attention of health care providers and political leaders at an international level.

One of the studies on which the IOM report was based was one conducted at Harvard [3] in the 1980's which concluded that nearly 4% of patients suffer some form of harm during a hospital stay, of which 70% suffered temporary damage and 14% resulted in death for the patient. It estimated that between 44,000 and 98,000 people die in hospitals each year as a result of adverse events (AE), figures that exceed mortality rates from traffic accidents, breast cancer or Acquired Immunodeficiency Syndrome (AIDS). The United Kingdom Department of Health, in its annual report of 2000, *An Organisation with a Memory*, estimated that AE occurs in nearly 10% of hospitalizations [4] however, in Australia, the AE rate was 16.6% among patients admitted to a hospital [5]. The cost of these events is quite high, and it is compounded by the erosion in patients' trust, safety and satisfaction.

Since then, a number of studies have been published on the frequency of AE linked to health care, their effect on patients, the potential impact on health systems and the need to study them; most studies have been conducted in a hospital setting [6-9], although experiences are emerging in other environments like primary care (PC) [10-13]. This has led to broader recognition of the problem, the inclusion of safety targets in strategic improvement plans in health organizations and more extensive research into the matter.

In 2006, the Ministry of Health and Social Policy (MSPS) presented its Quality Plan for the Spanish National Health System identifying better safety for patients in the care of the National Health System-see http://www.msps.es/organizacion/sns/planCalidadSNS/home.htm-as a strategy for fostering clinical excellence. Among other initiatives, financing was provided for the research projects "National Study on Adverse Effects Linked to Hospitalization. ENEAS 2005" [14] and "Study on Patient Safety in Primary Health Care. APEAS Study" [15]. The results of the latter study show that primary care practice in Spain is relatively safe, with a prevalence of AE of 18.63%, 70% of which are avoidable, with a predominance of mild cases. It is estimated that AE cases may affect 7 of every 100 people per year.

A cornerstone of the international movement for patient safety and an objective of the MSPS strategy is to foster a safety culture at all levels of health care with a proactive, preventive and educational management approach. Safety culture can be described as the common values, beliefs, behaviours, perceptions and attitudes held by the staff in a health center [16].

The WHO's World Alliance for Patient Safety created a working group with international experts to identify overall priorities in patient safety, with a prominent place for "poor safety culture" in the developed countries [17].

Multiple tools have been developed and evaluated to assess patient safety culture [18-24]. The choice among them will depend on their expected use, the target population, reliability, validity and other considerations [25].

Nearly all these tools sufficiently cover dimensions such as leadership, policies and procedures, professionals and communication and presentation of results [26]. Patient safety culture is a relatively new field [27] and a majority of the studies published on it are based on hospital studies [28]. Few studies have been done on patient safety culture in primary health care [26,29,30] and to date, none in Galicia.

Aside from this information and the existing antecedents, it has become necessary to deal with a crucial component in this entire machinery: medical professionals themselves. Medical professionals are the leading agents providing health care and they are responsible for a great deal of the organization's clinical and social outputs. Their attitudes and perceptions, their degree of involvement and commitment to collective challenges, their working environment and conditions, communication, workload and a huge variety of factors will result in either more or less safety for the patient. Thus, the implementation of a true patient safety culture in primary health services must be one of the main challenges faced in the immediate future, where training will play a key role.

Professionals are needed with knowledge and skills in areas like application of the best available evidence, communication and dialogue. They must perceive that the enhancement of care quality and of factors that help make health care safer are essential in the exercise of the profession.

Quite often, medical students or residents are not seen as an important part of ensuring patient safety. They are an unexploited resource for preventing medical errors, as they should be trained to recognize errors and speak openly about them as a tool for enhancing care quality and learning. Tutors must supervise and encourage students and residents to actively report errors or incidents they observe and prevent the intimidation of the medical hierarchy from frustrating their potential as safety advocates [31]. There are now certification systems in medical education that acknowledge the lack of training in patient safety and have included it among the basic skills [32].

In Spain, post-graduate education is provided through internal resident programs (MIR in Spanish) that must be successfully completed in order to practice the profession. The Family and Community Medicine teaching units (Medicina de Familia in Spanish) are the structures for planning and developing post-graduate education in the field. The present curriculum in the field, which was approved in 2004 [33], provides innovation as an educational assessment strategy with the development of the so-called Thoughtful Practice Guide, which includes a series of creative learning tools [34-36].

These tools are diverse and applicable to several educational areas: one of these is the self-audit [37] of clinical histories to investigate whether a certain care practice to be measured meets pre-defined and desired standards of quality. It is aimed at finding practical solutions to deficiencies. The very act of reflecting upon the results obtained and expected is educational; its educational potential has been recognized because it helps medical professionals become aware that their clinical practice is not perfect and that they need to improve on a continuous basis; it acts as a powerful motivational incentive by serving as a method of self-modifying conduct; it enables the identification of educational needs; it helps to improve the efficiency of clinical practice by detecting practices that are unnecessary or inconsistent with the professional's own standards, and contributes to improving the effectiveness of the health care provided to patients.

On the basis of the experience gained through participating in the APEAS, recording AE and the AE studies in primary care pediatrics of the Vigo health care area and in the Tuberculosis Unit, we hypothesize that action consisting of awareness-raising, recording, notification and handling of AE in medical own consultation is a formative assessment tool that meets the needs of adult learning by improving and promoting patient safety culture among participating professionals.

Given the need identified by the WHO and the MSPS for research into methods of learning and fostering patient safety culture among health organizations and professionals, we believe it is pertinent, timely and justified to undertake this research project into tools for enhancing patient safety culture in primary care by promoting awareness-raising and learning. Thus, we pose two hypotheses to be tested:

1. The registry of adverse events is a teaching tool that has a positive impact on patient safety culture in the Family and Community Medicine teaching units of Galicia.

2. The Hospital Survey on Patient Safety Culture (SOPS) is valid for use in primary health care services.

## Methods/Design

### Design overview

For the first hypothesis: Educational intervention study. Experimental unifactorial design of two groups-control and intervention-with pre-and post-test recording of the patient safety culture in Family Medicine teaching units with the SOPS (Additional file 1), as per residents' answers. In the intervention group, tutor training on patient safety will also be conducted, followed by the recording of adverse effects with the APEAS survey and feedback (Figure 1).

**Figure 1 F1:**
[figure not shown]
Summary of trial design

For the second hypothesis: Psychometric study of SOPS, including exploratory factor analysis, internal consistency and item analysis.

### Study setting and population

#### Setting

The Spanish National Health System is a system of universal coverage (including illegal immigrants). Services are free at the point of delivery, with the exception of prescription drugs to persons under 65 years of age, who should participate in paying with a contribution of 40% of retail, with some exceptions. The health powers are transferred entirely to the regions since late 2002. This decentralization resulted in 17 health departments (ministries or departments of health), the most common structure of regional health systems comprising a health department, responsible for regulation and policy planning, and a regional health service which is responsible for providing services. The territorial organization of health services is based on health areas; the primary care network is public and most of the providers are employees of public sector professionals. Primary care centers are staffed by a multidisciplinary team of family physicians, pediatricians, nurses and social workers, some also have physiotherapists, midwives, pharmacists, dentists and hygienists; they are assigned basic laboratory and diagnostic imaging, which can be found in the center or be centralized and serve several establishments.

Health expenditure reached U.S. $ 2,671 per capita (in PPP terms) and 8.5% of GDP in 2007, 71% is paid by public funds (collected mainly through taxes), which is intended to 16% primary care. The autonomous communities manage 90% of public health resources. In Galicia, with a population of 2,700,000, there are 7 areas of health, 398 primary care health centers and 3141 general practitioners, each of which serves on average 1500 citizens. Each of them has a training unit of Family and Community Medicine.

#### Population

Tutors belonging to the seven Family and Community Medicine teaching units of Galicia and residents in the last year of studies (MIR-4) of Family and Community Medicine.

In 2009, there were 160 tutors and 288 residents, of which 69 are MIR-4. As these residents and their tutors constitute the so-called "tutor-resident pair", we will request the participation of 35 tutors and 35 residents in the intervention group and 34 tutors and 34 residents in the control group.

### Measurements

#### Adverse events

The APEAS form (Additional file 2) was elaborated from the form created by the Medical School of the University of Washington in its project on patient safety and adapted after the results of the ENEAS study [14] with consensus techniques [15]. It consists of 11 modules that analyze the following: risk factors for the patient, a summary of the event and its possible cause, the care level at which it took place, its impact on the patient, the effects caused in the patient, the health care received by the patient as a result of the AE, the causal factors of the AE, the extent to which health care was the cause of the lesion, the evidence that the AE could have been avoided, an assessment of the evidence of possible prevention and what could have been done to prevent the problem. Although the study was conducted with the collaboration of PC professionals throughout the country without seeking a significant sample, it is of a seminal nature in Spain.

#### Culture

The SOPS consists of 44 questions and measures 14 dimensions. It was developed by Westat under contract with the Agency for Healthcare Research and Quality (AHRQ), and 16 of the questions were derived from a revision of existing instruments. The questionnaire was piloted in 20 hospitals, and the results were used to generate a list of 14 factors, all of which showed a high degree of internal consistency in factorial analysis (0.63 to 0.84). It emphasizes the institutional commitment to safety, transfers and transitions and teamwork. A summary of the technique and issues related to the development of the instrument and other tools is available http://www.ahrq.gov/qual/patientsafetyculture/.

### Intervention and randomization

#### Intervention

Intervention consists of three different moments, which will occur in this order:

##### a) Training workshops

Each participant is to be provided with current data on the incidence of adverse events in primary care and they will be acquainted with current initiatives in both Spain and internationally.

Program:

Theory: Introduction to patient safety; concepts of adverse effect, incident, adverse event, complication, secondary effect, adverse drug reaction; types of errors and their analysis; errors related to the use of drugs.

Practice: Manual recording of AE in the notification survey. The functioning of the form used in the APEAS will be presented and explained [15].

Duration

Each workshop will last approximately 2 hours.

Teacher team

The teacher team will be composed of two people, the same in the 8 workshops, one family doctor and a nurse.

Place and dates of workshops

One workshop will be conducted in each of the 7 health areas included, except in Lugo, where 2 will be given owing to the geographic dispersion of the learning centers, on their premises and with a timetable adapted to the centers' activity.

##### b) Recording adverse events with the APEAS form

Professionals in the tutor-resident pairs in the intervention group will manually complete, voluntarily and anonymously, the APEAS form whenever they identify an adverse effect in their offices during the recording period (15 days) in the course of their daily activities.

##### c) Feedback

Every participant will send the field coordinator the AE recorded along with data on daily activity in the forms. The field coordinator will, in turn, return to medical professionals the analysis of their records at the end of the study.

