### Measurement of results

For the first hypothesis, the dependent variable will be patient safety culture as measured by the SOPS. The independent or explanatory variable will be participation in the intervention-training workshops, recording of adverse events in daily work and reception of feedback.

For the second hypothesis, the following will be analyzed: reliability (internal consistency, repeatability), validity (content, criteria, construct) and change sensitivity (size of effect, paired t).

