### Phases of study

A working calendar of some 12 months was established for performing the study as such, followed by data analysis and dissemination of results.

In Phase 1 (first quarter), the main objective was to publicize the project and arouse interest so as to enable us to achieve a high degree of participation. Those interested were provided with detailed information on the process and the conditions.

The Family and Community Medicine teaching units throughout Galicia were contacted to invite tutors and residents to participate in the study. Participation was promoted by a drawing for a PDA and laptop computer among participants.

To ensure that participation in the study proceeds within a formal framework, each participant was sent a letter from the lead researcher in the project, along with an informed consent letter to be signed. A second letter was to be sent by the coordinator of field work, providing more specific details on the process and the phases of the study.

Based on the first version of the survey, the first phase included a review that will involve the participation of both experts and physicians, which might ensure that the wording of the questions was suitable. At the same time, all the materials necessary were prepared for the execution of the following phases.

The tutor-resident pair was assigned to each group-intervention or control-by simple random sample.

In Phase 2 (second quarter), a first use was made of the SOPS. This phase must was completed by both the control and intervention groups.

In Phase 3 (third quarter), an intervention was made in one of the groups pursuant to the protocol set forth above. In the control group, no action was taken.

In Phase 4 (fourth quarter), participants in both the control and intervention groups were again be provided with the SOPS to be filled out. The time between the two uses of the questionnaire was 4 months, an interval considered suitable, as it is too large for individuals to remember the answers given in the first phase and, at the same time, sufficient for the effect of the intervention to have been instilled and materialized in the daily work of medical professionals.

Phase 5 (third semester) was consist of a review of all the questionnaires, their encoding and recording in computer format and a statistical analysis of the data.

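### Feedback is part of the tested intervention, but its stated timing puts it at or after the only post-test, which conflicts with the phase plan

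*Protocol article*

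**What the plan says.** All references are to the protocol article.

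- **Design overview**: the intervention group receives tutor training, "followed by the recording of adverse effects with the APEAS survey and feedback".
- **Intervention**: "Intervention consists of three different moments, which will occur in this order". The three items that follow are workshops, recording with the APEAS form, and feedback.
- **c) Feedback**: participants send their records to the field coordinator, who is to "return to medical professionals the analysis of their records at the end of the study".
- **Measurement of results**: the explanatory variable for the first hypothesis is "participation in the intervention-training workshops, recording of adverse events in daily work and reception of feedback".
- **Phases of study**: "In Phase 3 (third quarter), an intervention was made in one of the groups pursuant to the protocol set forth above". In Phase 4, the fourth quarter, "participants in both the control and intervention groups were again be provided with the SOPS to be filled out". The study proper is given a calendar of about 12 months, with data analysis and dissemination afterwards. The two SOPS administrations are 4 months apart, and this interval is justified partly as long enough for the intervention to have taken hold in daily practice.

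**The concern.** A component can contribute to a randomised contrast only if it is delivered before the outcome is measured. Feedback is one of three named components and is written into the exposure whose effect is to be estimated. There is one post-intervention SOPS. If feedback comes after it, the between-group difference reflects workshop plus recording against no action, while the stated explanatory variable credits a package that also includes feedback.

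What is at stake is the label on the result. A positive finding would be credited to a package that had not been fully delivered when the outcome was taken. A null finding would be read as evidence against a package that was not fully tested. The article's reason for the 4-month interval would also not hold for feedback, because something given when the study ends has had no time to take hold by the post-test.

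**Working it through.** **Step 1. Put the sections on one calendar.** The inputs are the quarters and semesters in Phases of study, converted to months.

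| Event | Stated timing | Months |
|---|---|---|
| First SOPS | Phase 2, second quarter | 4–6 |
| Intervention | Phase 3, third quarter | 7–9 |
| Second SOPS | Phase 4, fourth quarter | 10–12 |
| End of the study proper | about 12 months | about 12 |
| Coding, data entry, analysis | Phase 5, third semester | 13–18 |
| Dissemination | Phase 6, fourth semester | 19–24 |

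**Step 2. Place feedback on it.**

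- *From c) Feedback*: the end of the study is about month 12. Any post-test date in months 10–12 is at or before that, so feedback falls at or after the post-test. Taking the study to run through Phases 5 and 6 makes it later still.
- *From Intervention and Phases of study*: feedback is the third part of an intervention made in months 7–9, so it precedes the post-test.

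The two placements differ by about 3 months (month 9 against month 12), and the post-test lies between them.

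**Step 3. Look for text that settles it.** Phase 3 is said to follow the protocol already described, but that description includes c) Feedback, so the reference leads back to the conflict. Phase 5 puts review, coding and analysis of the questionnaires after the post-test, and no earlier analysis of the APEAS forms is described. This leans towards the later placement but does not rule out a separate, earlier summary for participants. No sentence dates feedback relative to the Phase 4 SOPS.

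**Step 4. Consequence for sample size (illustration only).** The plan's own inflation reproduces: 24 / 0.90 = 26.7, rounded up to 27 per group. The base of 24 cannot be checked because no standard deviation or baseline is given.

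Assume a two-sided 5% comparison of two means with 80% power for the full three-part effect. The implied standardised difference is d = (1.960 + 0.842) × √(2/24) = 0.81. Let *f* be the share of that effect due to feedback and missed by the post-test. Then power = Φ(d(1 − f)√(n/2) − 1.960). The documents give no value for *f*, so a range is shown. The last column uses 34 per group, the smaller of the two invited groups, with no losses.

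| Assumed f | d reached | Power, 24 per group | Power, 34 per group |
|---|---|---|---|
| 0 | 0.81 | 80% | 92% |
| 10% | 0.73 | 71% | 85% |
| 20% | 0.65 | 61% | 76% |
| one third | 0.54 | 46% | 60% |
| one half | 0.40 | 29% | 38% |

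No figure stated in the plan changes. The table shows only how the result would depend on an unknown share.

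**The case against.** The best defence is that Phases of study places the intervention, without exception, in the third quarter and before the post-test. Feedback is by definition part of that intervention. The reasoning for the 4-month interval also presupposes that the intervention was complete. The end of the study, in a paragraph about handling the adverse-event records, might loosely mean the end of the recording exercise. This has weight: a reader might infer that the post-test cannot capture feedback, or that no intervention pair (of up to 35) received it in time, and the article does not establish either. What stands is that the literal words point the other way and nothing reconciles them.

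Three further inferences are tempting and should not be drawn.

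- **Anonymity.** The forms are completed anonymously, so a reader might infer that individual feedback was impossible. Participants send their own records to the coordinator, and coded or group feedback is compatible with the text. Anonymity also has no bearing on whether the post-test comes before or after feedback.
- **Loss of the reflective step.** The Background's passage on reflection concerns self-audit of clinical histories. The working hypothesis there lists awareness-raising, recording, notification and handling of events, and does not name feedback. The APEAS form itself asks about causes and prevention, so recording may prompt reflection.
- **An uninterpretable null result.** With late feedback, the randomised comparison still validly estimates workshop plus recording against no action. The fault would lie in the description of the package, not in the comparison.

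**Conclusion.** The point holds as a contradiction that must be reconciled, with a conditional consequence. Feedback belongs to the tested intervention under Design overview, Intervention and Measurement of results, and Phases of study puts that intervention before the post-test. Its own section gives a time that, on the article's 12-month calendar, is at or after the post-test.

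If that section was followed literally, one of three components was absent from the measured contrast, and the explanatory variable overstates what was tested. If the Phase 3 placement was followed, the contrast is as described and only the feedback wording is wrong. The documents do not say which happened. The conclusion therefore rests on the literal reading for its consequence, but not for the existence of the conflict. The size of any dilution is unknown, and the power figures rest on assumed shares and an assumed two-sided comparison of means.

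**What to change.** Reconcile c) Feedback, Measurement of results and Phases of study by stating when feedback was, or will be, sent relative to the Phase 4 SOPS.

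- **If feedback can still be scheduled**: return it after the 15-day recording period and before the post-test, and amend c) Feedback to say so. The cost is a quicker turnaround of the forms by the field coordinator.
- **If feedback came after the post-test**: remove "recording of adverse events in daily work and reception of feedback" as a single phrase from the explanatory variable, keep the recording part, drop the feedback part, and limit the conclusion to workshops plus recording. The cost is a wording change and a narrower claim.
- **If feedback came before the post-test**: correct the timing in c) Feedback and leave the explanatory variable as it is.

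Phases of study reports the fieldwork mostly in the past tense and describes dissemination as the present phase. Rescheduling is therefore probably no longer open, and the practical remedy is to report the feedback date and describe the tested package to match.
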